**Figure 1 F1:**
[figure not shown]
Schematic representation of the trial (MALTALEP study), together with the blood samples taken for analysis of host immune and gene profiles from subjects in the trial and in a non-intervention group (IDEAL study).

### Outcome measures

The primary outcome measure is the number of new leprosy patients emerging from the contact groups. The proportions between the two arms of the trial will be compared after one and two years.

Secondary data analysis will be carried out in order to define special groups at risk for developing leprosy and blood sample analysis of host immune and gene profiles.

### Intervention implementation and data collection

The medication provided in the trial is rifampicin. Rifampicin comes in capsules of 150 mg and the dosage is the same as recommended in the guidelines of the national leprosy control program of Bangladesh and RHP (Table 2). According to body weight and age, 2 to 4 capsules are taken by the contact under direct supervision of a RHP staff member.

**Table 2 T2:** Dosage of rifampicin chemoprophylaxis according to age and body weight

**Age/weight**	**Dose of rifampicin**
Adult >35 kg	600 mg
Adult <35 kg	450 mg
Child 10–14 years	450 mg
Child 5–9 years	300 mg

The vaccine provided in the trial is BCG. The BCG vaccine is applied by trained research assistants to all included contacts. 0.1 ml of BCG vaccine is given by intradermal injection. The BCG vaccine used in the trial (and in routine neonatal vaccination in Bangladesh) is produced at the Japan BCG Laboratory and is a freeze-dried glutamate BCG vaccine (Japan), composed of 0,5 mg/ampule live bacteria of Calmette-Guérin (as approximately 70% moist bacteria) and 2,0 mg/ampule sodium glutamate (as a stabilizer). Vaccines are stored at the State Immunisation Programme facilities.

All eligible patients and their contacts will be informed verbally about the study through the reading of the consent form, and then invited to participate. Before inclusion, the patient and their contacts are asked to sign a form if they agree to participate in the study. For illiterate people a thumb print will be taken, and for minors under 16 years of age, the guardian’s additional consent will be taken. Contacts explicitly give consent for BCG vaccination and SDR, and for blood drawing. Furthermore, the researcher has to sign that he/she has accurately read or witnessed the accurate reading of the consent form to the participants, that the individuals have had the opportunity to ask questions and they have given consent freely. Participants will also be informed that they will be offered free consultation and treatment in the case of adverse events following BCG vaccination. They are provided with a vaccination card with details on how to reach the researcher if they have any concerns. Also, participants are informed that their participation is completely voluntary and that they may choose not to participate or stop at any point of time. Their decision not to volunteer, or to refuse to answer particular questions, will not affect their relationship with the researchers or other staff members of RHP.

At the initial contact survey in the patient’s home, BCG will be given to all included contacts, followed by chemoprophylaxis with SDR two months later in those groups randomized to receive it (FU1). Follow-up examinations will be carried out one year (FU2) and two years (FU3) after receiving BCG. The three follow-up moments will be used to investigate whether the contact has developed leprosy or may be a suspected leprosy case (primary outcome measure). These patients will be sent to Nilphamari hospital or a local clinic for further investigation and treatment of leprosy. At these moments both groups will also be examined for adverse events following the BCG vaccination. Blood samples will be taken from 300 randomly chosen contacts for further molecular and immunological testing. Subjects not available for follow-up during the house visits will be contacted in order to plan another house visit. The trial started in July 2012 and will have duration of intake of 24 months. With a total observation period of 2 years after intake, the study will thus be completed after 48 months.

A separate database has been designed for the trial, which is linked to the database already in use at the RHP. Data are entered in the field onto purpose designed data sheets during clinic visits and contact group surveys. These data are sent to the RHP center in Nilphamari, where they are entered into the database. All paper forms are scanned and filed on hard disk and CD. The paper copies of the data will be retained for at least 15 years after completion of the study. An electronic copy of the database is sent to the department of Public Health of Erasmus MC in the Netherlands on a monthly basis. Modern back-up facilities are available at Nilphamari as well. Protection of privacy of patients in the database will be according to Erasmus MC standards.

### Blinding

Ideally, we would like to have set up a (double) blinded trial. However, this was not possible, since we have not been able to locate any company that could produce placebo tablets especially for this trial.

### Adverse effects

Rifampicin can give adverse events, such as gastro-intestinal complaints, skin rash, elevated liver enzymes, headache, dizziness, influenza-like syndrome, acute loss of kidney function, thrombocytopenia, asthma-like symptoms and shock [13]. Also, rifampicin can cause urine, saliva, tears and faeces to turn an orange or red colour. However, the chance of developing these symptoms is low, especially when giving a single dose of rifampicin only. In a previous trial, in which over 20,000 contacts of leprosy were given SDR, no adverse events were reported, apart from innocent red discoloration of the urine (for which the contacts were forewarned) [8,14].

Serious complications of BCG vaccination are uncommon. Although localized skin reactions occur frequently; less than one in 1000 people vaccinated develop significant local reactions, such as abscesses or regional lymphadenitis [14,15]. More serious adverse effects include osteitis, osteomyelitis and disseminated infection, but these are rare [16-18]. As many as 95% of BCG recipients have an insignificant, local reaction at the site of inoculation, however, lesions typically heal by three months with permanent residual scarring at the puncture site.

Both interventions (BCG and SDR), have separately been used widely in contacts of leprosy patients, with minimal adverse effects [8,19]. There is no reason to expect any serious difficulties from the combined interventions, as they will be given two months apart. However, strict monitoring of adverse events will take place in the trial. Leaflets containing information about the aims and the methodology of the trial, and describing potential adverse reactions will be given to all contacts included in the trial. These leaflets request that contacts report any suspected adverse reactions to the responsible researcher. The responsible researcher will then examine all contacts with reported adverse reactions. All contacts will also be examined two months, one year and two years after administration of the BCG vaccine. Data on adverse events is collected on the Contact Registration Forms of the trial. In the event of minor side effects, contacts will be referred to a State Tuberculosis Medical Officer for treatment, but the trial will not be stopped. In case of serious adverse effects the PI will stop the trial and initiate an individualized treatment scheme. All costs for treatment will be refunded.

### Data analyses

Statistical analyses will be done using SAS software. We use techniques for the analysis of survey samples to account for the clustering at the level of the index patient in the sample. Bivariate associations are investigated using “proc surveyfreq” and the Rao Scott χ2 instead of the Pearson χ2. We also use “proc surveylogistic” instead of the ordinary logistic regression procedure. We report odds ratios, but because of the low prevalence of the outcome these are comparable with relative risks. The number needed to treat (NNT) is calculated per subgroup of contacts. A significance level of 5% is used in all tests.

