## Background

The global number of new leprosy cases has remained constant over the past years [1], indicating that transmission of *Mycobacterium leprae,* the causative agent of leprosy, is ongoing in many endemic countries. The basic intervention is multidrug therapy (MDT) given to newly found leprosy cases, but this seems to be insufficient to decrease the number of new cases.

The main risk of exposure to *M. leprae* is in close contacts of new, untreated cases. Epidemiological studies have shown that the chance of finding a previously undiagnosed leprosy patient is ten times higher in household contacts of leprosy patients than in the general population, and the chance of finding leprosy among different categories of neighbors and social contacts is between three and five-fold [2,3]. Therefore, it has been suggested that contacts should be the main focus of a future leprosy control strategy. Such strategy should have three basic pillars: 1) case detection; 2) case management; and 3) contact management [4].

In the past years, many studies have investigated the use of immunoprophylaxis (vaccination) and chemoprophylaxis to prevent leprosy. These interventions have focused primarily on contacts of leprosy patients. Bacillus Calmette-Guérin (BCG) vaccination is known as a vaccine against tuberculosis and is routinely given to infants as part of the neonatal immunization scheme in many parts of the world. BCG is also recognized as protecting against leprosy [5,6]. Over the years several vaccine trials using BCG have been performed to establish its protective effect against leprosy, often in combination with *M. leprae* or related mycobacterium vaccines. BCG was as good as, or superior to the other mycobacterium vaccines [4].

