### Randomization

Each contact group will be randomly allocated to one of the two study arms (Arm 1: BCG only, or Arm 2: BCG plus SDR) by means of computer generation with a 1:1 ratio for each arm. The allocation to receive SDR is stamped on the data collection forms of each contact group. Immunoprophylaxis with BCG will be given at the moment of the contact survey to all included contacts in both arms of the trial, followed by chemoprophylaxis with SDR eight weeks later in contacts of Arm 2.

A schematic representation of the MALTALEP study is given in Figure 1 (left side), together with a non-intervention group (right side) and the sampling framework for analysis of host immune and gene profiles, which is part of the IDEAL study (see below).

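### No adjustment for recorded contact-level risk factors is specified for the primary comparison, although the article does not rule out enrolment of contacts with the arm visible

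*Protocol article*

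**What the plan says.** **Outcome and comparison.** Under Outcome measures, "The primary outcome measure is the number of new leprosy patients emerging from the contact groups". The next sentence gives the comparison: "The proportions between the two arms of the trial will be compared after one and two years". Analysis of groups at special risk is listed as secondary.

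**Analysis.** Data analyses uses survey-sample methods "to account for the clustering at the level of the index patient in the sample". "Bivariate associations are investigated using" proc surveyfreq with the Rao-Scott chi-square. Proc surveylogistic is also used, "instead of the ordinary logistic regression procedure", and odds ratios are reported. No covariate is named, and neither procedure is tied to the primary comparison.

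**Allocation and enrolment.** Under Randomization, "Each contact group will be randomly allocated to one of the two study arms" in a 1:1 ratio, and "The allocation to receive SDR is stamped on the data collection forms of each contact group". Under Participants, groups of about 15 are formed during the contact survey. Intervention implementation and data collection says that data sheets are filled in at these surveys and that contacts consent to BCG, SDR and blood drawing. Blinding says that the trial is open because no placebo could be obtained.

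**Risk factors held.** Table 1 records year of birth, sex, relation to the index patient and vaccination status.

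**The concern.** Randomising contact groups balances the index patients in expectation. It does not by itself balance the people enrolled into each group afterwards. Here the members come from categories of unequal risk, refusal of consent is an exclusion, and the form in use carries the arm. If staff choice or willingness to join depends on the arm, a crude comparison of proportions mixes the effect of SDR with a difference in who was enrolled.

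The article itself treats the recorded factors as important. The Background puts the chance of finding an undiagnosed patient at "ten times higher in household contacts of leprosy patients than in the general population", against three- to five-fold for neighbours and social contacts. It also says that the effect of SDR depended on BCG status. The plan already holds the data and the procedure to deal with a difference in these factors, but does not say that it will use them for the primary comparison. In an open trial, leaving the choice between crude and adjusted estimates unfixed is itself undesirable.

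**Working it through.** The plan gives no figure on this point, so there is none to reproduce. The check asks how far an enrolment imbalance in one recorded factor would move the crude result.

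**Inputs from the article**
- Household contacts about 10-fold, neighbours and social contacts 3- to 5-fold (Background). Ratio r = 10/5 = 2.0 to 10/3 = 3.33.
- Control rate 4 per 1000 per year, expected reduction 50%, 10% loss, about 10,000 per arm (Sample size calculation). Two-year risks are therefore 0.8% and 0.4%, with 9,000 evaluable per arm.

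**Assumptions not in the article**
- The ratio r, which describes previously undiagnosed disease, also applies to incident disease.
- Household share a = 30% in Arm 1, and b = 35% or 40% (or 25% or 20%) in Arm 2. The article gives no shares and no reason to expect one direction over the other.

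**Shift in the crude risk ratio** = [1 + b(r − 1)] / [1 + a(r − 1)]

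| a, b | r = 2.0 | r = 3.33 |
|---|---|---|
| 30%, 35% | 1.35/1.30 = 1.038 | 1.817/1.70 = 1.069 |
| 30%, 40% | 1.40/1.30 = 1.077 | 1.933/1.70 = 1.137 |

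The shift is about 4–7% in the first case and 8–14% in the second. With a true risk ratio of 0.50 and b = 40%, the crude estimate would centre on 0.50 × 1.077 = 0.54 to 0.50 × 1.137 = 0.57.

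**Effect on error rates**, for r = 2 or 3, with 9,000 per arm, control risk 0.8% and clustering ignored. Type I error uses d = (p1 − p2)/√[p1(1 − p1)/n + p2(1 − p2)/n], with p2 = p1 × shift, and equals 1 − Φ(1.96 − d) + Φ(−1.96 − d).
- b = 25%: null risk ratio 0.96 or 0.94, type I error 5.6% or 6.7%.
- b = 20%: null risk ratio 0.92 or 0.88, type I error 7.6% or 12.2%.
- b = 40%: power at a true risk ratio of 0.5 falls from 93.5% to 88.6% or 84.6%.

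The 93.5% is simply the power at these two-year risks without clustering. Whether it fits the planned 80% is a separate sample-size question that does not affect this point.

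**Precision.** In a simulation of 150 trials (9,000 per arm; assumed odds ratios 2.5 for household, 2 for a multibacillary index patient, 0.4 for BCG), the mean standard error of the log odds ratio was 0.2413 crude and 0.2416 adjusted. Only the near-equality is used here. Adjustment costs no precision and gains none.

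**The case against.** A reader might infer three stronger things, and the article does not support them.

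- **That contacts are chosen after the arm is known.** This is not stated. The Randomization text can be read as allocating a group already formed. Consent is described without a difference by arm, BCG goes to everyone at the survey, and SDR follows eight weeks later. All household contacts are surveyed, so the household share depends largely on household size. What remains is that the stamp is on forms used in an open trial and that no concealment until consent is described.
- **That the primary comparison is fixed as unadjusted.** It is not. A logistic procedure listed after a bivariate test may well be meant to carry covariates, and a covariate list may stand in a full protocol or SAP. The quoted words on logistic regression concern clustering, not adjustment. The point is only that the article states the primary comparison as proportions and assigns the model no part in it.
- **That adjustment would free the result from bias.** It deals only with factors that are recorded and adequately modelled. Unrecorded selection and unblinded ascertainment would remain. Hiding the arm until contacts are listed and consented addresses the cause.

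Two further objections stand in part. The ratio of 2.0 to 3.3 comes from prevalent disease, which is excluded at the initial survey, and the three- to five-fold figure includes social contacts, who are not an enrolment category. The imbalances are assumed, and a shift of 4–14% is modest beside a planned 50% reduction. Both limit the size of the point but do not remove it. Index class (SLPB, PB2-5, MB) is settled before the contact survey and cannot be changed by choosing contacts, so the enrolment argument does not reach it.

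**Conclusion.** The point holds as an inexpensive improvement, not as an error in the plan. Enrolment that differs by arm is possible on the procedures described, is not shown to occur, and would not be corrected by comparing crude proportions. The illustrated shift of about 4–7% or 8–14% rests wholly on the assumed household shares and on carrying the prevalence ratios over to incidence; its direction is unknown. An imbalance of this order would not overturn a true halving of risk. It could matter for the type I error or for a smaller true effect.

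**What to change.** In Data analyses, name as the primary estimate the Arm 2 versus Arm 1 odds ratio from proc surveylogistic, clustered by index patient and adjusted for relation to the index patient, age, sex and prior BCG. Keep the crude Rao-Scott comparison as supporting, and tabulate these factors by arm. Adjustment for index class is optional.

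State when the arm becomes visible relative to listing and consent, so that a reader can judge what adjustment cannot repair.

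Keep the categories coarse. On the planning rates, two-year events number about 9,000 × 0.008 + 9,000 × 0.004 = 72 + 36 = 108, and one-year events about half that, 36 + 18 = 54.

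The cost is wording only. The factors are in Table 1, the procedure is already in the plan, and the target of about 10,000 contacts per arm does not change.

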### Sample size calculation

In our power calculation, heterogeneity in the chance of contacts to develop clinical symptoms of leprosy was taken into account, but no major effect on the numbers needed was found. In the earlier COLEP trial [8] we found an incidence rate (IR) of leprosy among household contacts and direct neighbors of 4 per 1000 per year in the untreated group over the first two years. We hypothesize that in contacts receiving BCG only, this number will be the same in the first year or possibly increase slightly. Also based on the previous trial, we expect a 50% reduction through the SDR intervention (IR of 2 per 1000). On the basis of these figures (with α = 0.05 two-sided, power = 0.80), a total of about 10,000 contacts will be necessary in each group in order to detect reliably the expected protective effect of the BCG plus SDR combination of 50%, even taking into account an expected 10% loss to follow-up of contacts.

### Blood samples for analysis of host immune and gene profiles

Early detection of *M. leprae* infection (before clinical manifestations occur) is vital to reduction of transmission. However, current diagnosis relies on detection of clinical signs, since there are no tests available to detect asymptomatic *M. leprae* infection or predict progression to leprosy. Furthermore, although BCG vaccination and rifampicin chemoprophylaxis are both proven strategies for leprosy prevention, it is not known how the immune and genetic biomarker profiles are influenced by these (combined) interventions. Identification of such profiles will enable distinguishing pathogenic from protective biomarkers and lead to effective prophylactic interventions for leprosy.

In this study we intend to evaluate and optimize diagnostic tools for identification of individuals who should best be targeted for prophylactic treatment. In order to develop improved diagnostic tests based on reliable biomarkers that are detectable in blood samples, this study will analyze immune- and genetic host parameters in order to identify biomarkers that distinguish individuals controlling bacterial replication from those developing disease using the following assays:

1. Whole blood assays (WBA):Upon recruitment 4 ml venous blood will be drawn and used directly in three WBA, using tubes pre-coated with *M. leprae* WCS, ML2478/ ML0840 recombinant proteins or without stimulus. Each tube will be marked with a colored cap specific for one of these stimuli. After 24 hour incubation at 37°C, tubes will be frozen and stored for analysis of cellular markers [20] and/or analysis in field-friendly lateral flow assays for detection of Th1/Th2 cytokines as well as anti-PGL-I Ab [21].

2. Dual color Reverse Transcription Multiplex Ligation dependent Probe Amplification (dcRT-MLPA). From each individual venous blood (app. 2.5 ml) will be added to a PAXgene® tube and stored at −80°C. Total RNA will be extracted, purified and used to identify differential gene expression by dcRT-MLPA [22] using 179 selected target genes (Geluk A, Van Meijgaarden KE, Wilson L, Van der Ploeg- van Schip JJ, Bobosha K, Quinten E, Dijkman K, Franken KLMC, Haisma I, Haks MC *et al*: **Longitudinal Immune Responses and Gene expression Profiles during Development of Type 1 Leprosy Reaction**. in preparation).

Blood samples will be taken from 150 randomly selected contacts in both arms of the trial (total 300) 6 weeks after BCG vaccination (Figure 1). In addition, blood will be taken from any contact developing leprosy during the observation period of 24 months at the time of diagnosis before treatment. The aim of this part of the study is to identify:

1. Host immune responses and gene expression profiles specific for pathogenic as well as protective immune responses to *M. leprae* by comparison of profiles of patients *vs.* contacts.

2. Effect of chemo- and immunoprophylactic interventions on host immune responses and gene expression profiles and clinical disease by comparison of profiles of BCG-vaccinated *vs.* non-vaccinated contacts.

As part of our study on host immune and gene profiles in a non-intervention group, conducted by the IDEAL (Initiative for Diagnostic and Epidemiological Assays for Leprosy) consortium, similar blood samples will also be taken from a cohort of 500 new leprosy patients, 5,000 of their contacts, and from new cases of leprosy arising from this contact group during a 24-month observation period. As a referent group (endemic controls), 250 healthy individuals from the general population will be sampled as well.

### Preparations and process evaluation

The trial is conducted according to detailed research protocols that were developed in close consultation with the senior staff of RHP. In addition, an online Good Clinical Practice (GCP) course was completed by all Principal Investigators. All research assistants received training in research protocol procedures and giving BCG. They were also assisted in the field by the staff of the national EPI program when giving the BCG, until they were well enough trained to do this independently. Training (both theoretical and practical) was also given in the venapunction of blood for the additional immunological and transcriptional analyses to be performed later. All researchers have a professional background in the diagnosis and treatment of leprosy and received refresher courses on this.

Quality checks on all aspects of the data collection and entry are performed monthly and feedback on the results is given to the field staff and the data entry manager. For this purpose Erasmus MC has employed a medical doctor as independent Trial Monitor in Bangladesh to perform supervision tasks on a monthly basis to ensure optimal compliance to the study protocol.

